# ICT-based system to predict and prevent falls (iStoppFalls): study protocol for an international multicenter randomized controlled trial

**DOI:** 10.1186/1471-2318-14-91

**Published:** 2014-08-20

**Keywords:** Fall prevention, Fall risk assessment, Older adults, Exercise, Strength, Balance, Exergames, Video games

## Abstract

**Background:**

Falls are very common, especially in adults aged 65 years and older. Within the current international European Commission’s Seventh Framework Program (FP7) project ‘iStoppFalls’ an Information and Communication Technology (ICT) based system has been developed to regularly assess a person’s risk of falling in their own home and to deliver an individual and tailored home-based exercise and education program for fall prevention. The primary aims of iStoppFalls are to assess the feasibility and acceptability of the intervention program, and its effectiveness to improve balance, muscle strength and quality of life in older people.

**Methods/Design:**

This international, multicenter study is designed as a single-blinded, two-group randomized controlled trial. A total of 160 community-dwelling older people aged 65 years and older will be recruited in Germany (n = 60), Spain (n = 40), and Australia (n = 60) between November 2013 and May 2014. Participants in the intervention group will conduct a 16-week exercise program using the iStoppFalls system through their television set at home. Participants are encouraged to exercise for a total duration of 180 minutes per week. The training program consists of a variety of balance and strength exercises in the form of video games using exergame technology. Educational material about a healthy lifestyle will be provided to each participant. Final reassessments will be conducted after 16 weeks. The assessments include physical and cognitive tests as well as questionnaires assessing health, fear of falling, quality of life and psychosocial determinants. Falls will be followed up for six months by monthly falls calendars.

**Discussion:**

We hypothesize that the regular use of this newly developed ICT-based system for fall prevention at home is feasible for older people. By using the iStoppFalls sensor-based exercise program, older people are expected to improve in balance and strength outcomes. In addition, the exercise training may have a positive impact on quality of life by reducing the risk of falls. Taken together with expected cognitive improvements, the individual approach of the iStoppFalls program may provide an effective model for fall prevention in older people who prefer to exercise at home.

**Trial registration:**

Australian New Zealand Clinical Trials Registry Trial ID:
ACTRN12614000096651.

International Standard Randomised Controlled Trial Number:
ISRCTN15932647.

## Background

In the next decades a rise in the proportion of people aged 65 years and older is expected
[1,2]. Successful independent living in older people can be compromised by a number of key health conditions including heart disease, stroke, diabetes, and falls
[3]. About one third of community-dwelling older people falls at least once a year
[4], increasing to half of people aged 80 years and over
[5]. Falls can be devastating, contributing to a considerable increase in mortality and morbidity
[6]. It is therefore crucial to invest in research aimed at dealing with health challenges of an ageing population such as fall prevention. The prevention of falls and its serious consequences (e.g., hip fracture) may enable older people to live independently, maintain their quality of life, and reduce health care costs
[7].

Several systematic reviews and meta-analyses have provided robust evidence to support interventions for preventing falls in older people
[8,9]. Exercise interventions are one of the single most effective strategies for preventing falls
[10]. Systematic review evidence suggest that, to be effective in preventing falls, exercise programs must include at least moderately-challenging and progressive balance exercises and be performed frequently (i.e., for more than 50 hours over the course of the intervention period)
[10]. Despite evidence of the benefits of exercising, several barriers have been identified that affect participation such as unsuitable schedules of group sessions, insufficient means of transport to get to training facilities, lack of time to exercise due to other social commitments, and feelings of loneliness and isolation
[11]. More research on alternative approaches for delivery of exercise programs is needed to address the challenges and improve adherence to exercise programs, especially for older people and more socially deprived people who are at the highest risk of falling. Novel and engaging methods have great potential to enhance long-term motivation and adherence without increasing costs.

The proposed intervention will investigate the effects of an individually tailored ICT-based exercise program delivered through the home television set, called iStoppFalls (
http://www.istoppfalls.eu). The results will allow evaluation of the intervention regarding feasibility and acceptability, quality of life, as well as effectiveness on fall risk factors in older people.

## Methods/Design

### Participants

One hundred sixty community-dwelling older people aged 65 years and older will participate in this international, multicentre, single-blinded, two-group randomized trial (Figure 
1). Study sites are located in Cologne, Germany (n = 60), Valencia, Spain (n = 40), and Sydney, Australia (n = 60). Participants will be recruited between November 2013 and May 2014. Older people will be enrolled if they meet the following eligibility criteria: (1) aged 65 years and older, (2) living in the community, (3) able to walk 20 m without a walking aid, (4) able to watch television (TV) with or without their glasses from 3 m distance, and (5) have enough space for system use (3.5 m^2^). The exclusion criteria are: (1) insufficient language skills to understand the study procedures, (2) cognitive impairment (Mini-Cog: 1–2 recalled words and abnormal clock drawing test)
[12], and (3) medical conditions (i.e., uncontrolled hypertension, severe neurological disorder, acute cancer, psychiatric disorder, acute infections) that prevent participation in a regular exercise program. A medical clearance form has to be issued by the participant’s medical doctor to confirm medical suitability for the intervention program.

**Figure 1 F1:**
[figure not shown]
Flow chart of study design.

### Randomization and blinding

Following successful baseline assessments, participants will receive a unique computer-generated random number for identification (ID). A research assistant will then allocate the participants’ ID to the intervention or control group (ratio 1:1) by using permuted block-randomisation (software available from
https://apps.neura.edu.au/blinders/). Couples (participants living in the same household) will be treated as one unit and randomised into the same block. Reassessment will be performed by experienced and trained research assistants (RA) who are blinded to group allocation. To avoid unblinding of the RA, participants will be reminded not to talk about their user experience during the reassessments.

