#### Statistical analyses and sample size

A priori power analysis has been conducted for PPA as the primary outcome by using data from a previous study. The estimated sample size of 52 participants for the individual study sites in Cologne and Sydney is based on a large effect (f = 0.40) for the PPA (ANCOVA, alpha 5%, power 80%, numerator df 1, number of groups 2, number of covariates 1)
[57]. With an anticipated dropout of 15%, 60 participants will be recruited. The sample size will be sufficient for determining clinically significant between-group and within-group differences as well as main interaction effects in the continuously-scaled physical and cognitive outcome measures. For this study the intention-to-treat method will be used. Data on feasibility will be analysed using descriptive techniques. Student t-tests (for continuous variables with normal distribution), Fisher's exact test (for nominal data, small sample size), and Mann–Whitney U test (for ordinal or continuous data without normal distribution) will be used to determine differences between the intervention and control group at baseline. Analysis of covariates (ANCOVA) will be used to determine the intervention effect on outcome measures at follow-up adjusting for baseline values. Negative binomial regression will be used to test for differences in fall rates between groups. Paired t-tests and repeated measures ANOVA will be used to analyse changes within groups and to explore subgroups (e.g., different doses) in the intervention group. The alpha level will be set at 5%. Analyses will be performed with SPSS version 23 for Windows (SPSS, Inc., Chicago, IL). Reporting of the trial will follow CONSORT
[58] statement for non-pharmacological interventions and the SPIRIT
[59] guidance for protocols of clinical trials.

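### Couples are randomised as one unit, but the named models and the sample size treat every participant as independent, and the same-block wording conflicts with joint allocation

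*Protocol article*

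**What the plan says.** The Randomization and blinding section sets a 1:1 ratio. A research assistant will "allocate the participants’ ID to the intervention or control group (ratio 1:1) by using permuted block-randomisation". For people who share a home it adds: "Couples (participants living in the same household) will be treated as one unit and randomised into the same block".

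The Statistical analyses and sample size section names the between-group models. ANCOVA "will be used to determine the intervention effect on outcome measures at follow-up adjusting for baseline values". For falls, "Negative binomial regression will be used to test for differences in fall rates between groups". Neither sentence mentions the household.

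The sample size is 52 for each of Cologne and Sydney, from a large effect (f = 0.40) on the Physiological Profile Assessment (PPA), with these settings: "ANCOVA, alpha 5%, power 80%, numerator df 1, number of groups 2, number of covariates 1". Then: "With an anticipated dropout of 15%, 60 participants will be recruited". No expected number of couples, within-couple correlation or design effect is given. Across the three sites, "One hundred sixty community-dwelling older people aged 65 years and older will participate".

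**The concern.** There are two linked problems.

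**Analysis unit.** The article fixes the couple as the unit that is randomised, then names models and a sample size that count each partner as a separate independent observation. Partners share a home, and the intervention is delivered through the home television, so some positive correlation in adherence and outcome is plausible. When partners are in the same arm, that correlation makes the independence standard error too small, the confidence interval too narrow and the true type I error higher than 5%.

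**Allocation wording.** In 1:1 permuted-block randomisation each complete block contains both arms. Being in the same block is therefore not the same as being in the same group, and the second half of the couples sentence does not deliver what the first half promises. Staff who follow the literal text could put a control participant, who is meant to keep to usual exercise habits, in a home where the system is installed. Analysis cannot undo that exposure.

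**Working it through.** **Inputs from the article:** f = 0.40, alpha 5%, power 80%, numerator df 1, two groups, one covariate, 52 per site, 15% dropout, 60 recruited (Statistical analyses and sample size); 160 in total (Participants).

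**Inputs assumed, because the article gives neither:** p, the share of participants enrolled as one of a couple, 0.1 to 0.4; ρ, the within-couple correlation of the baseline-adjusted outcome, 0.1 to 0.5.

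**1. The plan's own figure.** The noncentral F power uses λ = f²N with 1 and N − 3 degrees of freedom. At N = 52, λ = 0.16 × 52 = 8.32 and power is 80.7%; at N = 51 it is 79.9%. So 52 reproduces exactly, with no allowance for clustering. The 60 matches 52 × 1.15 = 59.8. After 15% dropout, 60 × 0.85 = 51 remain, so the per-site calculation has no reserve.

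**2. Partners in the same arm.** Take an arm of n people with residual variance σ². It contains pn/2 couples, and each adds 2ρσ² to the variance of the sum. The variance of the arm mean is then (σ²/n)(1 + pρ). Hence:

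- design effect DE = 1 + pρ
- true standard error ÷ independence standard error = √DE
- type I error of the unadjusted test = 2[1 − Φ(1.96/√DE)]
- power and required N: step 1 with λ divided by DE

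| p | ρ | DE | √DE | Type I error | N per site for 80% | Power at 52 |
|---|---|---|---|---|---|---|
| 0.1 | 0.1 | 1.01 | 1.005 | 5.11% | 52 | 80.3% |
| 0.2 | 0.2 | 1.04 | 1.020 | 5.46% | 54 | 79.2% |
| 0.3 | 0.3 | 1.09 | 1.044 | 6.05% | 56 | 77.3% |
| 0.4 | 0.5 | 1.20 | 1.095 | 7.36% | 61 | 73.3% |

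Simulating the plain ANCOVA at N = 52 (20,000 runs) gave 5.5% for p = ρ = 0.2 and 6.3% for p = ρ = 0.3. At N = 160 the same settings gave 5.1% and 5.9%. DE does not depend on N, so pooling the sites does not remove the inflation. Power is a per-site matter only: at N = 160 and f = 0.40 it is 99.9% before any design effect.

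**3. Partners in opposite arms.** The covariance now reduces the variance of the between-group difference, and the factor becomes 1 − pρ. At p = ρ = 0.3 it is 0.91 and the type I error of the unadjusted test is 4.0% (3.8% simulated at N = 52). The test is conservative.

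**4. What same-block placement implies if each partner takes a separate slot.** In a block of size b, the chance that two people get different arms is (b/2)/(b − 1): 1/1 = 100% for b = 2, 2/3 = 67% for b = 4, 3/5 = 60% for b = 6. Block size is not stated, so these values are illustrations of the literal reading only.

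**5. Does the obvious remedy work at this size?** In simulation at N = 52 with same-arm couples, a household-clustered standard error with no small-sample correction and a 1.96 cut-off rejected 6.1-6.8% of the time. Plain ANCOVA rejected 5.3-6.4% for p = ρ between 0.1 and 0.3. With a small-sample correction and a t reference, the clustered analysis rejected about 4.7-5.5%.

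**The case against.** The best defence has four parts.

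- **This is a condensed article.** It names model families, and a household term could sit in an analysis plan that is not shown. That is possible. But the article itself states both the unit of randomisation and the models, and as named they do not match; the sample size it reports in full has no clustering allowance. This part of the defence lowers the severity but does not remove the point.
- **One unit means one allocation.** On this reading *block* is a poor choice of word for *group*, and the split chances in step 4 describe a procedure that was not intended. This is the likelier meaning. A reader might infer that the protocol has a rule that splits couples; the text does not support that. It supports only that the two halves of the sentence conflict and that the literal wording permits a split.
- **The size is assumed.** The PPA combines contrast sensitivity, proprioception, sway, knee extension strength and hand reaction time. Nothing in the article suggests that partners correlate near 0.5 on these after baseline adjustment, and the effect could be close to nil. This stands.
- **Partners may not share equipment.** A reader might infer that a couple uses a single exercise system. The article says that intervention participants are provided with the equipment and that activity is tracked for each participant; it does not say what a couple receives.

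A reader might also add the two harms together. They are alternatives: for any one couple, either the partners share an arm and the standard error is too small, or they are split and it is too large. The paired t-tests and repeated measures ANOVA are within-group analyses, so they do not bear on the randomised contrast.

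**Conclusion.** The point holds at moderate severity. The article makes the couple the unit of randomisation, while its named ANCOVA, negative binomial model and sample size take no account of it. Provided partners share an arm and their adjusted outcomes correlate positively, the type I error lies between about 5.1% and 7.4% over the assumed range. It stays near 6% or below when p and ρ are both at most 0.3, and reaches 7.4% only with 40% of participants in couples and a correlation of 0.5. These figures are for the ANCOVA; no separate figure was derived for fall rates.

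The allocation wording is a separate contradiction that needs no assumed numbers. It leaves even the direction of the error open: anti-conservative if couples are kept together, conservative and with an exposed control partner if they are split.

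**What to change.** - In Randomization and blinding, replace the same-block phrase with *allocated to the same group (one allocation per household)*.
- Record a household ID in the dataset.
- Fit the ANCOVA with a household random intercept, or with household-clustered standard errors that use a small-sample correction and a t reference. Without the correction, the clustered version is no better at per-site size than the plain ANCOVA in the modest cases.
- Fit the negative binomial model with household-clustered standard errors, likewise corrected.
- State the expected share of couples beside the sample size, so that a reader can see whether 52 per site still suffices.

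The cost is one phrase, one variable and a model option with its correction. The downside is slightly wider intervals if couples are common: from √1.01 = 1.005, about 0.5%, to √1.20 = 1.095, about 9.5%, over the assumed range. If couples are few, the results barely change.

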### Study design

The iStoppFalls system consists of a technology-supported fall prevention program and a fall risk assessment. Based on discrete measuring technologies the system predicts the individual fall risk, offers a tailored and targeted exercise program, and provides individual feedback to the participant. For the iStoppFalls project, custom fall prevention software has been developed. The iStoppFalls software platform consists of new video game-based exercises and exergames focussing on balance and muscle strength, and a fall risk assessment. After randomization, the participants in the intervention group will be provided with a personal computer (Shuttle Barebone Slim-PC), a Google TV set top box (STB) by Sony, a Microsoft Kinect, a Senior Mobility Monitor (SMM) by Philips, and a Nexus 7 Android tablet.

Research staff will install the system components in participants’ homes. During the home visit of about two hours, participants will receive an introductory lesson in system use and an instruction manual. Participants will receive a follow-up home visit approximately two weeks after the installation to ensure safe use and progression of training, and to discuss any issues related to using the program. Additional home visits will be offered as needed or requested. The control group will follow their habitual exercise routine. Each participant will be provided with an educational booklet about general health and falls. Participants will be assessed at baseline (0 weeks), after 8 weeks, and at the end of the intervention period (16 weeks).

Adherence will be monitored by the iStoppFalls system which tracks the exercise activity of each participant. Falls frequency will be monitored with monthly fall diaries in control and intervention participants for 6 months after randomisation. A fall will be defined using the internationally derived consensus definition of ‘an unexpected event in which the participant comes to rest on the ground, floor, or lower level’
[13]. If the calendars are not returned, filled out incorrectly, or show non-adherence, participants will be contact by phone by a blinded (falls) and unblinded (adherence) RA, respectively. Participants will receive individual training reminders in the middle and the end of each week via the iStoppFalls system. Additionally, participants will be reminded by an unblinded RA to perform at least one interactive fall risk assessment (including questions about fall history and self-administered physical tests of balance, reaction time, and strength) each month.

Participants will be required to give written informed consent prior to inclusion. Ethical approval was obtained by the ethics committees of the German Sport University Cologne (24.09.2013), the Polytechnic University of Valencia (19.12.2013), and the Human Research Ethics Committee of the University of New South Wales (reference number HC12316, 19.12.2013). This trial will be conducted according to the ethical standards of the Helsinki Declaration.

### The iStoppFalls system

Participants interact with the system via the TV which is functionally extended by an android-based STB and a custom iStoppFalls application. The STB communicates with the iStoppFalls exergame software installed on the PC (Figure 
2). The application was designed using an exergame approach, and will be used for the exercises and fall risk assessments. The Microsoft Kinect (3D depth sensor) and the custom-made SMM (3D accelerometer, barometer), which is worn as a necklace, will monitor the participant’s performance during the assessments and exercises. In addition, the SMM is used for continuous mobility monitoring (i.e., walking distance, sit-to-stand transfer performance)
[14].

**Figure 2 F2:**
[figure not shown]
**iStoppFalls hardware system components.** AIT: Austrian Institute of Technology, DB: database, DVB: digital video broadcasting, HDMI: high definition multimedia interface, IR: infrared, KBS: knowledge based system, LAN: local area network, LDB: local database, PC: personal computer, SMM: Senior Mobility Monitor, STB: set top box, TV: television, USB: universal serial bus, USI: University of Siegen, WLAN: wireless local area network.

Participants control the movements of a virtual avatar with the Microsoft Kinect. The posture of the avatar is defined by the skeleton model of the Kinect Software Development Kit after applying filters to avoid jerky movements
[15]. Tracked motions, joint angles, and postures will be further used to define the real-time feedback for the users who will be informed about the distance walked (in meters) equivalent to their body movements
[16,17]. All aggregated data are transmitted to a knowledge-based system (server) for automatic data analysis and feedback generation. The participants will be able to monitor their results continuously via the STB over their interactive TV or tablet at home. An integrated social media platform will enable users to interact with each other and share their results.

#### Design of intervention

Following system installation, participants allocated to the intervention group will conduct a 16-week exercise program focusing on improving static balance, dynamic balance, and muscle strength for the lower extremities. The training content is based on best practice recommendations for exercise to prevent falls in older people by Sherrington et al.
[10,18]. It will be recommended that the participants perform at least three balance sessions of about 40 min each (including each of the exergames) and at least three muscle strength sessions of about 15 to 20 min each (including all strength exercises) per week. Participants are recommended to perform 10 min of balance exercises before each strength training session. The weekly training duration should therefore total to about 120 min for balance training and 45 to 60 min for strength training (resulting in approximately 50 h over 16 weeks). Participants will be recommended not to do strength training sessions on consecutive days. When balance and strength training is combined, participants will be instructed to start with the balance session. The prescribed exercise intensity is moderate to high varying according to the level of difficulty, number of repetitions, and additional ankle cuff weights (1 kg or 2 kg) used. Participants in the intervention group who decide to discontinue the exercise program may still continue to send in the monthly falls calendars and perform the reassessments.

